## METHODS

**Participants.** All newly admitted patients, men and women, referred to the GDH program (of the MGH) who meet eligibility criteria will be invited to participate. Participants must be able to understand study requirements (Mini Mental State Exam, MMSE >22/30) and to read and speak English or French. Participants with the following criteria: BMI >35 kg/m^2, presence of kidney (GFR <30 mL/min/SA), liver or heart failure, stroke in the last 6 months (unless totally recovered), Parkinson's disease, severe neurologic conditions, active malignancies, acute inflammation (CRP >10 mg/L), known diagnosis of hyperparathyroidism, recent acute weight loss (>10% in 3 months, unless stabilized), allergy to milk and/or fish, long-term use of corticosteroids or anti-neoplastic medication, will be excluded from the study. All subjects taking vitamin D supplements  $\geq$  800 IU/d will be asked to reduce their dose to 400 IU/d. If vitamin D supplements were prescribed, the subjects' physician will be informed to change the current prescription to 400 IU/d for the study duration. As for subjects taking any type of omega-3 supplements, they will be asked to cease it for the study duration. All eligible subjects will be approached by the study coordinator and will be provided with an information brochure. Subjects interested in participating will be invited to review study procedures and sign the consent form.

**Study design.** This is a randomized, placebo-controlled, double-blinded pilot trial of two parallel arms. Participants will be randomly assigned to one of two groups: experimental (EXP) or control (CTR). Randomization will be achieved by computer-generated permuted block of 4 with stratification according to sex. Research staff and participants will be blinded to group allocations.

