**Intervention.** Participants will be screened and baseline measures will be performed within their first 3 visits to the GDH. Upon randomization, EXP group will ingest a supplement of flavored whey protein isolate with added pure leucine (3 g) twice daily, before breakfast and before bedtime. Doses are adjusted per body weight as follows: 20 g, 25 g or 30 g per category of <65 kg, 65-75 kg and >75 kg of body weight respectively (see Appendix Table 2 for nutritional details). Supplements will be offered during 8 weeks (average time of GDH program attendance) and for the following 8 weeks, at home or residence, for a total of 16 weeks. The CTR group will ingest an isocaloric placebo consisting of 30 g maltodextrin (a simple carbohydrate, providing 116 kcal), following the same schedule. Both products will be provided in pre-weighted doses in sterile containers; participants will be instructed to dilute and mix with 125 mL (1/2 cup) water to ingest. The fish oil + vitamin D supplement will be provided as a liquid oil (NutraSea Liquid® from Ascenta). Participants will receive a dosing cup, pre-marked to measure 7.5 mL, providing 1500 IU vitamin D3 + 1125 mg EPA + 750 mg DHA, to be ingested once daily. CTR participants will receive an isocaloric placebo oil (corn oil) to be ingested similarly. Oil supplements may be mixed with the protein or maltodextrin powders or ingested separately according to taste. Participants already taking vitamin D (at lower doses than indicated in exclusion criteria) or omega-3 FA supplements may take part in the study but will be asked to interrupt their supplements for the duration of the study. Compliance will be evaluated by twice-weekly monitoring during GDH visits and frequent phone calls during the

second half of study, by self-reporting in a logbook and return of all empty containers and extra oil; ingestion of 80% of provided doses will be required to remain in the study.

**Outcomes: all outcomes (except body composition) will be measured at baseline (prior to intervention), 8 weeks (last program visit) and 16 weeks (returning visit).**

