Omega-3 fatty acids: Typical side effects include fishy aftertaste and burping, but these possible effects will be minimized by the choice of fish oil supplement NutraSea (from Ascenta) that is fruit-flavored (grapefruit/tangerine or apple). There is no UL determined for *n*-3 FAs. However, the European Food Safety Authority has established that supplemental doses up to 5 g/day “do not raise safety concerns for adults”. Our proposed daily dose of 2 g is less and has been used in several other studies in older adults, of longer duration.

*Potential risks:* as with any change in diet, dietary supplements may be associated with gastrointestinal adaptations at the onset (e.g. constipation or softer and more frequent stools), which typically resolve with time. If persisting, these will be addressed by dietary recommendations from the PI or graduate student (both RDs) or prescription of laxatives (by the study MD). The functional tests proposed are standard and specific to the geriatric population, will be performed by trained physiotherapists of the GDH and should cause no harm. Any serious and non-serious adverse event will be recorded.

*Financial compensation:* participants will not receive an honorarium for this study. Their transport or parking fees for the three assessment visits (baseline, 8 weeks and 16 weeks) at the Royal Victoria Hospital (Glen site) will be reimbursed.

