## Appendix

**Table 1. Information on Dietary Supplements to be used**

| Supplement and ingredients                                                                                | Brand Name/Company                                             | Health Canada NPN | Daily Dose ingested                                                                                                   | UL                                    |
|-----------------------------------------------------------------------------------------------------------|----------------------------------------------------------------|-------------------|-----------------------------------------------------------------------------------------------------------------------|---------------------------------------|
| Experimental supplement                                                                     |                                                                |                   |                                                                                                                       |                                       |
| Whey protein isolate (vanilla flavored)

- Protein (27g/30g dose)
- Vitamin D3 (100 IU/30g dose) | New Zealand Whey Protein Isolate/ The Protein Company ATW Inc. | 80054732          | 2 x 20 g = 40 g
2 x 25 g = 50 g
2 x 30 g = 60 g

36 g
45 g
54 g

66.7 IU
83.3 IU
200 IU | N/A

4000 IU/d                  |
| Leucine                                                                                                   | ProteinCo Leucine Powder/ The Protein Company ATW Inc.         | 80062837          | 2 x 3 g = 6 g                                                                                                         | 550 mg/kg/d                           |
| Fish oil containing vitamin D (flavored) :
- EPA
- DHA
- Vitamin D3                              | NutraSea +D/ Ascenta                                           | 80050462          | 7.5 mL oil =

1125 mg
750 mg
1500 IU                                                                      | EPA + DHA :
5 g/d

4000 IU/d |

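### The participant blind is not secured as written: both active products have a stated flavour and neither placebo does, which matters chiefly for the liquid oil

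*Protocol*

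**What the plan says.** The Study design paragraph of the Methods claims a double blind: "Research staff and participants will be blinded to group allocations".

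**Active products.** The Intervention paragraph says that "EXP group will ingest a supplement of flavored whey protein isolate with added pure leucine (3 g) twice daily". Appendix Table 1 names the flavour: "Whey protein isolate (vanilla flavored". For the oil, Table 1 has "Fish oil containing vitamin D (flavored", and the omega-3 paragraph under Ethical Considerations specifies "NutraSea (from Ascenta) that is fruit-flavored (grapefruit/tangerine or apple". The same paragraph states: "Typical side effects include fishy aftertaste and burping". It adds that the choice of a flavoured product is meant to minimise these effects.

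**Placebos.** For the powder, "The CTR group will ingest an isocaloric placebo consisting of 30 g maltodextrin", on the same schedule. For the oil, "CTR participants will receive an isocaloric placebo oil (corn oil) to be ingested similarly". Table 1 lists maltodextrin and corn oil and gives no flavour for either.

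The only statement on taste that covers both arms is under Ethical Considerations, where the whey, leucine and maltodextrin powders are together described as sweet. No section mentions matching of flavour or smell, or a check on whether the blind held.

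**The concern.** A placebo blinds the participant only if it cannot be told from the active product in use. Here the products are taken by mouth daily for 16 weeks, and the protocol's own product descriptions differ on flavour.

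Apart from feasibility, the primary outcomes are the 6-minute walk with gait speed, the 30-second chair-stand, Timed-Up-and-Go, handgrip and knee-extension strength. All depend on how hard the participant tries; the walk is self-paced. Someone who believes they are on the active supplement may try harder, and someone who believes they are on placebo may try less or take fewer doses. Adherence to supplements is itself a primary feasibility measure, and the Intervention paragraph makes 80% intake a condition of staying in the study. A belief about allocation could therefore affect retention as well as test results.

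The second objective is to supply pilot data for testing superiority over placebo, and the Statistical Analysis section uses those data to confirm the sample size of the full trial. A weakness in the blind would carry over to the full trial if the same products were used.

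**Working it through.** No figure in the plan is under test. The check sets the product descriptions side by side and asks which differences a participant could perceive.

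| Product | Flavour stated | Stated match to the other arm |
|---|---|---|
| Active powder | Flavoured (Methods, Intervention); vanilla (Table 1) | – |
| Placebo powder | None (Methods; Table 1); described as sweet together with the active powders (Ethical Considerations) | Isocaloric, same schedule, same containers and dilution |
| Active oil | Flavoured (Table 1); fruit (Ethical Considerations); none given in Methods | – |
| Placebo oil | None (Methods; Table 1) | Isocaloric, taken in the same way |

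**1. Exposure.** The regimen lasts 16 weeks × 7 = 112 days. At two powder doses a day this is 112 × 2 = 224 powder doses, and at one oil dose a day 112 oil doses, per fully compliant participant. Any perceptible difference is met many times.

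**2. The oil.** It is a liquid measured in a dosing cup, not a capsule, so it is tasted. Taken as listed, the active oil differs from corn oil in two ways: the added fruit flavour, and whatever fishy aftertaste the flavouring does not cover. A participant need not compare the two oils to notice the second. It is enough to know that the active oil is fish oil. The protocol makes that knowledge likely, since it excludes people with fish allergy and asks users of omega-3 supplements to stop taking them.

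**3. The powder.** Both powders are called sweet, both come in pre-weighed doses in the same kind of container, and both are mixed with the same volume of water. In a parallel design each participant tastes only one of them. A sweet drink, with or without vanilla, does not by itself reveal the arm. The stated flavour difference is real, but its power to unblind is much weaker than the oil's.

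**4. What is exposed.** The performance and strength outcomes are exposed throughout, and adherence possibly. Recruitment rate is not, because it is settled before anyone tastes a product.

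**5. Size.** The bias would depend on how many participants identify their arm beyond chance and on how far belief shifts each test. The documents give neither figure, so no magnitude is offered.

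**The case against.** **Silence is not denial.** The protocol nowhere says that the placebos are unflavoured. Table 1 lists ingredients, brands, licence numbers, doses and upper limits; it is not a masking specification. A reader might infer that the placebos are plain, that participants can taste their arm, and that the blind is lost. The documents do not support any of these as fact. They support only that flavour is specified on one side and not on the other. That is still more than missing detail, because anyone buying the products as listed would obtain two oils that differ in taste.

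**The fruit flavour is there to mask the fish.** This is its stated purpose, and it should reduce the aftertaste. The protocol promises to minimise the effect, however, not to abolish it, and a fruit flavour in one arm only is itself a difference. The oil may be mixed into either powder, which could help to hide it, but this is optional and left to the participant's taste.

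**It is a pilot, not powered for group differences.** This is correct. With 40 participants split equally, the standard error of a difference in means is √(1/20 + 1/20) = 0.32 SD, so sampling error in the efficacy estimates will be large in any case. Bias of this kind, however, does not shrink with a larger sample, and a pilot is the cheapest place to find and remove it.

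**Acceptance of the real product is part of what is studied.** This also stands: taste-related adherence in the active arm is a legitimate feasibility result. It is the comparison between arms that suffers.

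A reader might also infer that staff are unblinded through the returned containers and leftover oil. The documents do not say who handles the returns or whether those people run the tests, so that step is not supported.

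**Conclusion.** The point holds in a limited form. The protocol claims blinded participants, specifies a flavour for both active products and for neither placebo, and describes a match that leaves out taste and smell. As written, the participant blind is not secured. The oil is the main reason and the powder a minor one. The consequence is possible expectation bias, of unknown size, in the pilot estimates on effort-dependent tests, and possibly in adherence.

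This rests on two assumptions: that the products are supplied as listed, with no unstated flavouring of the placebos, and that participants know fish oil is part of the active supplement. If the placebos are in fact flavour-matched, the problem reduces to a missing statement. It does not undermine the feasibility aim as a whole, but it is worth correcting because the repair is simple.

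**What to change.** In the Intervention paragraph of the Methods and in Appendix Table 1, specify that the corn oil carries the same fruit flavour as the active oil (whichever of the listed flavours is dispensed) and that the maltodextrin carries the same vanilla flavour as the whey. If only one can be done, the oil should come first.

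Optionally, ask participants once, at the week-16 visit, which arm they think they were in, and report the answers by arm. Asking at the end avoids prompting them to work it out during treatment. The answers need cautious reading, since a late guess may also reflect perceived benefit.

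If a taste match cannot be achieved, qualify the double-blind claim and say so when the performance and strength results are reported.

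The cost is flavouring for about 20 control participants (half of the planned 40), plus one question at an existing visit if the guess is collected. The limitation is that no flavoured corn oil will match fish oil perfectly, so some risk to the blind remains.

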#### **OBJECTIVES**

Implementing the proposed nutritional supplement in the routine care of GDH participants will:

1. test the feasibility, acceptance and compliance to the supplement and its safety
2. provide pilot data to test the superiority of the supplement versus an isocaloric placebo on measures of muscle mass, strength, physical performance, and mobility.

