### ***Primary outcome measures***

- ◆ Feasibility: recruitment rate ( $\geq 50\%$ ), adherence to assessment tests ( $\geq 80\%$ ), adherence to supplements ( $\geq 80\%$ )
- ◆ Physical performance from validated tests:
  - 6-minute walk test: distance achieved at normal walking pace for 6 minutes, measured on a 30 m-course; gait speed is also measured during the first 4 m, in m/s. This test assesses the submaximal level of functional capacity and is indicative of mobility limitations; a change of 20 m has clinical relevance.
  - 30-second chair-stand: number of times capable to stand up completely and sit down within 30 seconds, without the aid of armrests (measured in number of chair-stands).
  - Timed-Up-and-Go (TUG): time required to rise from a chair, walk 3 m, turn and come back to sit on the chair, (measured in seconds).
- ◆ Muscle strength:
  - handgrip strength measured with hand-held dynamometer, measured seated, 3 measurements per hand, alternatively (measured in kg)
  - Maximal leg strength (isometric knee extension peak torque) from a 60-degree angle using the Biodex System 4 Pro dynamometer on the dominant side (measured in N).

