### **STATISTICAL ANALYSIS**

This is a pilot study designed to generate data on feasibility, acceptance and compliance to the supplement and study tests; it is not powered for identifying statistical differences in the main outcomes. The sample size required for the full study will be of approximately 160 participants (80 EXP, 80 CTR). This calculation is based on an expected difference of 1 second in reducing the chair-stand time between the 2 groups, acknowledging that the CTR will also gain from the rehab program, and from standard deviation from published studies. This sample size should be enough to detect differences in handgrip and leg strength and in appendicular muscle mass accretion. Pilot data will therefore be crucial to confirm these calculations. We aim to recruit 40 participants to provide confidence intervals to determine the final RCT sample size.

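### The 80% intake rule removes participants after randomisation at the same cut-off as the primary adherence criterion, and may cost week-8 and week-16 data

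*Protocol*

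**What the plan says.** In the protocol's METHODS, the Intervention paragraph states that "ingestion of 80% of provided doses will be required to remain in the study". Intake is judged after allocation, from checks at day-hospital visits, telephone calls, a logbook and returned containers. The paragraph does not say when the 80% is judged: continuously, at week 8, or on the 16-week total.

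Under Primary outcome measures, the first outcome opens with "Feasibility: recruitment rate" (at least 50%). It adds adherence to the assessment tests (at least 80%) and "adherence to supplements" (at least 80%). For the last of these the text gives no denominator, and it does not say whether the figure is a mean intake or a share of participants.

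The OBJECTIVES are to "test the feasibility, acceptance and compliance to the supplement and its safety" and to "provide pilot data to test the superiority of the supplement versus an isocaloric placebo". STATISTICAL ANALYSIS adds: "We aim to recruit 40 participants to provide confidence intervals to determine the final RCT sample size".

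No section says that a participant below 80% is still assessed at weeks 8 and 16.

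**The concern.** There are two problems.

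First, the condition for staying in the trial and the threshold for success are the same number on the same variable. A reader of the results could not tell whether an adherence figure of 80% or more describes the patients or the retention rule.

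Second, the rule is an exclusion made after randomisation. The allocation method ("Randomization will be achieved by computer-generated permuted block of 4 with stratification according to sex") makes the arms comparable at entry. Removing people for what they do afterwards can undo that, because the product can influence intake. The protocol itself mentions satiety from protein (BACKGROUND), and fishy aftertaste and gastrointestinal effects (ETHICAL CONSIDERATIONS).

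At stake are the adherence result, the safety record of those who tolerate the product least well, and the estimates meant to plan the full trial. An analysis plan can define a denominator or an analysis set, but it cannot recover assessments that were never done.

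**Working it through.** The 80% threshold is not a computed quantity, so there is no figure of the plan to reproduce. The full-trial size of 160 plays no part here. The inputs from the protocol are the 80% retention rule, the 80% criterion and the 40 participants. Everything else below is marked as assumed.

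**1. Can the adherence criterion fail?** Take the rule and the criterion to cover the same period and the same products.

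| Denominator | Mean intake below 80%? | Share reaching 80% below 80%? |
|---|---|---|
| Those who remain | No, each value is at least 80% | No, always 100% |
| All randomised | Yes | Yes |

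Illustration, assuming that 12 of 40 fall short:
- All randomised: 28/40 = 70%, Wilson 95% CI 55% to 82%. The criterion is missed.
- Those who remain: 28/28 = 100%, Wilson 95% CI 88% to 100%. The criterion is met.

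The same holds for mean intake. Assume that individual intake follows a beta distribution with mean m and concentration 4, and simulate samples of 40:

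| True mean m | P(mean over all 40 is at least 80%) | Average of the mean among those at 80% or more |
|---|---|---|
| 70% | about 0 | 90% |
| 75% | about 5% | 91% |
| 80% | about 51% | 92% |

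As a check for m = 75%: the individual SD is √(0.75 × 0.25/5) = 0.194 and the SE of the mean is 0.194/√40 = 0.031. The distance to 80% is 0.05/0.031 = 1.6 SE, an upper tail of about 5%.

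**2. Which assessments can be lost?** This depends on the timing, which is not stated.
- Removed before week 8: both later assessments.
- Removed between weeks 8 and 16: the week-16 assessment.
- Judged on total doses at week 16: possibly none.

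**3. Precision.** If a share d of the 40 is removed equally from both arms and the outcome SD is unchanged, standard errors grow by 1/√(1 − d).

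| d (assumed) | Remaining of 40 | Rise in SE |
|---|---|---|
| 10% | 36 | 1/√0.9 = 1.054, about 5% |
| 20% | 32 | 1/√0.8 = 1.118, about 12% |
| 30% | 28 | 1/√0.7 = 1.195, about 20% |
| 40% | 24 | 1/√0.6 = 1.291, about 29% |

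**4. Bias in the between-arm difference.** Let f be the share removed in an arm, and δ the amount by which those removed would have done worse than those retained. The retained mean exceeds the full-arm mean by f × δ. With no true effect, the apparent difference is f(EXP) × δ(EXP) − f(CTR) × δ(CTR).
- Equal shares and equal δ: 0.
- Assumed 30% v 15%, δ = 0.5 SD in both arms: 0.15 × 0.5 = 0.075 SD.
- Assumed 30% v 15%, δ = 0.8 SD in both arms: 0.15 × 0.8 = 0.12 SD.

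For scale, with 20 per arm (an equal split of 40) the SE of a difference is √(2/20) = 0.32 SD. These shifts are therefore about 0.24 to 0.38 of one standard error in the pilot.

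**The case against.** The strongest reply has four parts.

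- **The criterion need not pass automatically.** A reader might infer that the adherence endpoint is met by construction. The protocol does not say that adherence is computed among those who remain, and denominators are often left to an analysis plan. If every randomised participant counts, a removed participant is a failure and the criterion can be missed. This stands, so the point is conditional on the denominator.
- **Adherence is not unknowable.** A reader might also infer that the pilot cannot learn its adherence rate. A participant can be removed only because low intake was recorded, so the number removed is known and the rate over all randomised can be recovered. This stands too: the risk is a misleading report of information that exists.
- **The loss of assessments depends on timing.** It cannot be said that every removed participant misses both visits. Nor does the effect on the assessment-adherence criterion have a fixed direction: counting removed participants as missed lowers it, and leaving them out does not.
- **The bias may be nil.** Both arms take a powder and an oil, both powders are described as sweet, and the trial is double-blind, so similar removal is plausible. The pilot also claims no power for efficacy.

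These points limit the strength of the claim but do not justify the rule. Nothing in the protocol keeps a removed participant under observation, and neither a chosen denominator nor an all-randomised analysis set brings back tests that were not performed.

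**Conclusion.** The concern holds in conditional form. The protocol removes participants after randomisation on a variable that treatment can affect, at the cut-off that also defines success on a primary feasibility outcome. Among those retained the criterion cannot fail; over all randomised it can, and the text does not choose. Under either reading, later performance, strength and safety data may be lost for those removed early.

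The one size that can be given is for precision: standard errors larger by about 5% to 29% if 10% to 40% are removed, assuming equal removal and an unchanged SD. A reader might infer that the treatment comparison is biased by a definite amount. The documents do not support that: they give neither removal rates by arm nor outcomes of low-intake participants, and the bias is zero if removal is equal and like-for-like. The 0.075 to 0.12 SD above only illustrates assumed inputs.

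**What to change.** Delete the condition "ingestion of 80% of provided doses will be required to remain in the study" and state instead that:

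- every randomised participant stays in follow-up for the week-8 and week-16 assessments and for adverse-event recording, whatever their intake;
- supplement adherence is computed over all randomised participants;
- performance and strength are analysed as randomised;
- intake of at least 80% only defines a secondary compliers analysis.

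This concerns follow-up and analysis only. It does not touch doses or the decision whether a participant continues the product.

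The cost is a short protocol amendment and up to two extra assessment visits for each participant who would otherwise have been removed. Reported adherence may look less favourable, but it will describe the patients whom the full trial would randomise.
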